**Sample size considerations**

For sample size calculations various parameters need to be specified. These include the intracluster correlation (ICC) and the cluster autocorrelation (CAC). The ICC refers to the correlation between values from individuals in the same cluster on the same occasion. The CAC measures the correlation between means within the same cluster at different times. It is assumed that data for each standard are collected according to the incomplete stepped wedge design shown in Figure 1, with three clusters following each sequence in the design. Sample size calculations were performed to determine differences detectable using the Rshiny app which was developed by [name], a Professor of Biostatistics whose research is focused on the design and analysis of stepped wedge trials (available at: <https://clusterrcts.shinyapps.io/rshinyapp/>).

Table 4 indicates the percentage change in compliance for the standard that is detectable for a single standard, with either 80% or 90% power, an ICC of either 0.1 or 0.2, and a CAC of 0.8 or 0.5 using a sample of 25 clients for each assessment month in each cluster. These calculations focused on the proportion of respondents who deemed the standard to have been achieved as a binary response, assuming that the initial compliance level for the standard is 50%.

**Table 4 Differences detectable (percentage) for using an incomplete stepped wedge design with specified number of facilities conducting a standards-based audit in a balanced incomplete stepped wedge design**

| **Sample size for each facility-month** | **Number of facilities doing standards-based audit** | **ICC** | **CAC** | **Power** | |
| --- | --- | --- | --- | --- | --- |
|  |  |  |  | **80%** | **90%** |
| 25 | 12 | 0.1 | 0.5 | 21.1% | 24.0% |
|  |  |  | 0.8 | 18.3% | 20.9% |
|  |  | 0.2 | 0.5 | 26.0% | 29.3% |
|  |  |  | 0.8 | 20.9% | 23.9% |
| 25 | 18 | 0.1 | 0.5 | 17.5% | 20.0% |
|  |  |  | 0.8 | 15.2% | 17.5% |
|  |  | 0.2 | 0.5 | 21.6% | 24.7% |
|  |  |  | 0.8 | 17.5% | 20.0% |
| 10 | 18 | 0.1 | 0.5 | 21.7% | 24.7% |
|  |  |  | 0.8 | 20.5% | 23.5% |
|  |  | 0.2 | 0.5 | 25.6% | 28.9% |
|  |  |  | 0.8 | 23.0% | 26.1% |

These calculations indicate that there will be at least 80% power to detect an improvement in compliance of 22% provided the ICC does not exceed 0.2 and the CAC does not fall below 0.5. If the initial compliance level is lower or higher than 50% then the difference detectable will be smaller. For standards that are audited in fewer clients per cluster or in fewer clusters the difference detectable will be larger. To indicate the impact of each of these reductions in sample size the differences detectable are also provided for 10 clients per cluster with 18 facilities and for 25 clients per cluster with 12 facilities auditing the standard.

**Statistical Analysis**

Each standard considered will be analysed separately to provide an estimate of the impact of the audit of that standard on compliance with the standard. Analysis will use the binary responses of respondents within facilities in multilevel mixed effects logistic regression models, with fixed effects for intervention and facility type, and random effects for month, facility (cluster) and month by facility (cluster) interaction. District will also be considered for inclusion as a random effect. For each standard the impact of the intervention will be estimated with a 95% confidence interval. Compliance with defined standard of care, aggregated for all standards audited will also be estimated in a similar manner, with a 95% confidence interval.

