**Figure 1: Schematic representation of measurements of compliance with a single standard by sequence and month of study**

| Sequence | Stratum | Month | | | | | | | |
| --- | --- | --- | --- | --- | --- | --- | --- | --- | --- |
|  |  | July | Aug | Sept | Oct | Nov | Dec | Jan | Feb |
| 1 | I | 0 |  | 1 |  |  | 1 |  |  |
| 2 | II |  | 0 |  | 1 |  |  | 1 |  |
| 3 | III |  |  | 0 |  | 1 |  |  | 1 |
| 4 | I | 0 |  |  | 0 |  | 1 |  |  |
| 5 | II |  | 0 |  |  | 0 |  | 1 |  |
| 6 | III |  |  | 0 |  |  | 0 |  | 1 |

0 denotes assessment of compliance with the standard under the current standard of care.

1 denotes assessment of compliance after taking action to improve the quality-of-care delivery for the standard

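### Month is a random effect although Figure 1 ties intervention status to calendar month, so a secular trend is only partly removed from the intervention effect

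*Protocol*

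**What the plan says.** The Statistical Analysis section of the protocol sets out a multilevel logistic model for each standard "with fixed effects for intervention and facility type, and random effects for month, facility (cluster) and month by facility (cluster) interaction". District may be added as a further random effect. No fixed period effect or time trend appears there or elsewhere. The aggregate over all standards, which is the primary outcome, is to be estimated along the same lines, so it takes over the same treatment of month.

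Figure 1 gives the design for one standard: six sequences in three strata over eight months. Its key reads "0 denotes assessment of compliance with the standard under the current standard of care" and "1 denotes assessment of compliance after taking action to improve the quality-of-care delivery for the standard". The Sample size considerations section builds on that layout and puts three facilities in each sequence: "It is assumed that data for each standard are collected according to the incomplete stepped wedge design shown in Figure 1".

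**The concern.** No sequence in Figure 1 returns to control, so exposure rises with calendar month:

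- July and August: control assessments only.
- September to December: both conditions, but always in different strata.
- January and February: intervention assessments only.

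The comparison protected by randomisation is therefore the same-month comparison between strata in September to December. A random month effect assumes that month effects are independent of intervention status and shrinks them towards a common mean. The design breaks that assumption. The shrinkage lets the uncontrolled before/after contrast back into the estimate. If compliance moves over the eight months for reasons common to all facilities, such as season or other quality initiatives, part of that movement is reported as an audit effect, with an interval that is too narrow for it.

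**Working it through.** **Inputs.** Figure 1 with three facilities per sequence (6 × 3 = 18 facilities); "using a sample of 25 clients for each assessment month in each cluster"; "with either 80% or 90% power, an ICC of either 0.1 or 0.2, and a CAC of 0.8 or 0.5"; and, for the starting level, "assuming that the initial compliance level for the standard is 50" percent. Two-sided alpha of 0.05 is my assumption, taken from the 95% confidence interval. Linear drift of 0 to 5 percentage points per month is also assumed, because the protocol gives none.

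**Model for the check.** Generalised least squares on facility-month means with total variance σ². Two months in the same facility share covariance σ²·ICC·CAC. Each facility-month adds σ²[ICC(1−CAC) + (1−ICC)/25]. The SE of the intervention effect is the root of its diagonal element in (X′V⁻¹X)⁻¹.

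**Step 1: reproduce Table 4.** The detectable difference d solves d = (1.960 + 0.842) × s × √v. Here s is the SE per unit SD and v is the average of p(1−p) under the two conditions. For 18 facilities, ICC 0.2 and CAC 0.5:

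- Fixed months: s = 0.1619. At d = 0.216, v = (0.25 + 0.716 × 0.284)/2 = 0.2267, so d = 2.802 × 0.1619 × 0.4761 = 0.216. Table 4 states 21.6%.
- No month term: s = 0.1029. At d = 0.141, v = (0.25 + 0.641 × 0.359)/2 = 0.2401, so d = 2.802 × 0.1029 × 0.4900 = 0.141.

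18 facilities, 25 clients, 80% power:

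| ICC, CAC | Table 4 | Fixed months | No month term |
|---|---|---|---|
| 0.1, 0.5 | 17.5% | 17.4% | 11.4% |
| 0.1, 0.8 | 15.2% | 15.0% | 9.4% |
| 0.2, 0.5 | 21.6% | 21.6% | 14.1% |
| 0.2, 0.8 | 17.5% | 17.3% | 10.6% |

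The 12-facility rows and the 90% column also agree within 0.2 points under fixed months.

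**Step 2: how far exposure follows time.** Number July as 0 and February as 7. Control cells have mean month 2.0 and intervention cells 5.0.

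**Step 3: bias with no true effect.** Bias = Σ wᵢ × drift × monthᵢ, where w is the intervention row of (X′V⁻¹X)⁻¹X′V⁻¹ and σ² = 0.25. With fixed months the weights sum to zero within each month, so any calendar pattern common to facilities cancels. For random months I set the month variance to what the drift implies: the sample variance of 0 to 7 is 6, so 6 × drift². Type I error is the chance that the estimate exceeds 1.96 model SEs, given that bias.

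| ICC, CAC | No month term, 1 point/month | Random, 1 point/month (type I) | Random, 2 points/month (type I) | Fixed |
|---|---|---|---|---|
| 0.1, 0.5 | 3.3 | 3.1 (10%) | 5.2 (17%) | 0 |
| 0.1, 0.8 | 3.4 | 3.1 (12%) | 4.9 (20%) | 0 |
| 0.2, 0.5 | 3.3 | 3.2 (9%) | 5.7 (15%) | 0 |
| 0.2, 0.8 | 3.4 | 3.2 (11%) | 5.3 (19%) | 0 |

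**Step 4: month variance estimated, as a fitted model would do.** REML on facility-month means, 500 simulated trials per setting, no true effect, random months:

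| Drift (points/month) | ICC 0.1, CAC 0.8: bias (type I) | ICC 0.2, CAC 0.5: bias (type I) |
|---|---|---|
| 1 | 3.0 (14%) | 3.0 (9%) |
| 2 | 5.7 (40%) | 5.7 (20%) |
| 3 | 7.5 (57%) | 7.8 (36%) |
| 5 | 7.8 (46%) | 11.1 (52%) |

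With no drift, random months are unbiased and reject in 5-6% of trials. At 1-2 points/month the month variance is estimated as zero in about half the trials, and the model then makes no time adjustment. Fixed months in the same simulation give bias of −0.8 to +0.2 points and rejection of 5-8% at every drift from 0 to 5.

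**Step 5: where fixed months cannot work.** Within stratum I the observed months are July, September, October and December, and the intervention indicator equals September plus December. The design matrix (four months plus intervention) has 5 columns and rank 4. The same holds in strata II and III.

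**The case against.** The strongest reply is that the harm rests on a trend the protocol does not state. Without drift there is no bias, and 2 points/month means 14 points from July to February (7 × 2). This stands as a limit on the size, not on the mechanism: staggered start months are there so that the analysis need not assume a flat calendar.

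Random period effects can also be defended where months are plausibly exchangeable. Here exposure rises with month by design, so that defence does not carry over.

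On Table 4, the protocol does not state the time model of the app; I infer it. The 10-client rows match less well (19.8-24.3% computed, 20.5-25.6% stated, at 80% power). Planning on a more conservative model than the analysis is not itself an error. The mismatch is supporting evidence only.

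A further objection stands in full: fixed months are not feasible for every standard. Facilities choose their standards, and some may be audited in few facilities or in one stratum only.

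Two stronger readings are tempting. A reader might infer that any secular improvement passes wholly into the intervention effect. It does not: at 5 points/month 46-68% of the bias from ignoring month remains, because a larger estimated month variance moves the fit towards fixed effects. A reader might also name the training workshops as the source of drift. The Randomisation section places each stratum's workshop before its first audit cycle, so it precedes every assessment in that stratum. Its effect would follow time since workshop, which fixed calendar months would not fully remove.

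**Conclusion.** The point holds. The protocol states a model that gives only partial protection against calendar trend, in a design where intervention status follows the calendar. This is a stated choice, not detail left to a SAP. For one standard at 18 facilities and 25 clients, with no true effect, the bias is 0 without drift, about 3 points at 1 point/month (type I error roughly 9-14%) and about 5-6 points at 2 points/month (roughly 15-40%). The upper figures depend on ICC and CAC and on whether the month variance is estimated. All sizes rest on the assumed linear drift and on a linear model for facility-month means, so they approximate the planned logistic model. The pooled primary analysis shares the mechanism, but I put no size on it. Nothing in the protocol shows that a trend will occur or that the result will be false. What it shows is that the planned model would not reliably separate a trend from an audit effect.

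**What to change.** In the Statistical Analysis section, replace the random month effect with fixed categorical effects for the calendar months observed, and keep the random facility and facility-by-month effects. Apply this to the pooled primary analysis and to each single-standard analysis whose facilities span more than one stratum, after checking that at least one month holds both conditions. For a standard audited in one stratum only, the intervention effect is aliased with month; report it descriptively as an uncontrolled before/after change.

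The change needs no new data. It costs precision: with no drift and 18 facilities, the SE is about 5.5 against 3.4 points at ICC 0.1 and CAC 0.8, and 8.1 against 5.2 at ICC 0.2 and CAC 0.5. At 12 to 18 facilities this is the precision that the 25-client rows of Table 4 already imply. Sparser standards fare worse: with one facility per sequence (six in all) the SE is about 14 points at ICC 0.2 and CAC 0.5.

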# **Methods**

Study design:

A Cluster randomised incomplete stepped wedge trial for multiple standards on obstetric Care will be applied to assess the impact of using standards-based audit on compliance with defined standards for emergency obstetric and newborn care in Malawi. To appropriately reflect the diversity of expert opinion and disciplinary perspectives, a set of standards around emergency obstetric and newborn care were developed using a systematic, participatory process in accordance with WHO process of developing guidelines^15^ . The standards were mainly developed to address the common obstetric and newborn causes of death in low resource settings (cite). There are 25 standards in 7 groups (subsequently referred to as Standards Groups A, B, C, D, E, F and G) which have been defined (Appendix 1)

A total of 44 facilities are included in the design comprising of 10 designated to provide Comprehensive emergency obstetric care CEmOC and 34 facilities designated to provide basic emergency obstetric care (BEmOC) health facilities. Each participating facility is a cluster, and each facility will implement two periods of standards-based audit cycles. Each audit cycle comprises three months (a quarter): an assessment month, a month for action to address issues and a re-assessment month. Each of the ten CEmOC facilities will complete two standards-based audits in each quarter (four standards in total) and each of the 34 BEmOC facilities will complete one standards-based audits in each quarter (two standards in total).

Each standard assessed will be assessed using the incomplete stepped wedge design shown in Figure 1. Up to three facilities will be assigned to each sequence.

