**Primary outcome measure**

Compliance with defined standard of care aggregated for all emergency obstetric and newborn care standards audited. This will be defined as the mean across all facilities and standards, with each standard audited by each facility carrying equal weight. (Thus, at facility level the means for CEmOC facilities which audit twice as many standards will carry twice the weight of the BEmOC facilities). Standards will be weighted by the number of facilities which audit the standard).

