**Data Collection**

As indicated in Figure 1 each of the standards to be audited at a facility will be assessed during the first and third month of the audit cycle for that standard. In addition, it will also be assessed during the first month of the first audit cycle at the facility (if the audit cycle is in the second quarter) or during the last month of the second quarter (if the audit cycle is in the first quarter) but not during other study months. Tables 2 and 3 illustrate the assessments to be performed for standards audited within a CEmOC facility in stratum which is assigned to audit for standards denoted as standards A, B, C and D, and a BEmOC facility in stratum II which is assigned to audit for standards denoted as standards E and F.

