**Target number of participants**

For each standard audited at a facility it is anticipated that care received by 25 clients will be assessed in each of three study months (as illustrated in Figure 1 and Tables 2 and 3). At each of the ten participating CEmOC designated facilities four standards are to be audited, thus the total clients participating at each CEmOC is expected to be 300. At each of the thirty-three participating BEmOC designated facilities two standards are to be audited, thus the total clients participating at each BEmOC is expected to be 150. The total number of participants is thus expected to be 8,100.

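### The primary pooled analysis is defined only by reference to a single-standard model, so the effects carried over include no term for standard or facility-by-standard; this costs precision and leaves the interval's coverage uncertain in either direction

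*Protocol*

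**What the plan says.** Statistical Analysis first describes a separate analysis of each standard. It uses "multilevel mixed effects logistic regression models, with fixed effects for intervention and facility type". The random part consists of month, facility and their interaction, and district may be added to it. The pooled outcome then gets one sentence: "Compliance with defined standard of care, aggregated for all standards audited will also be estimated in a similar manner". A 95% interval is promised there too. No term is added for the pooled case, and none is ruled out.

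Primary outcome measure makes the pooled quantity the primary one, "defined as the mean across all facilities and standards, with each standard audited by each facility carrying equal weight".

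The Methods section has each of 10 CEmOC facilities audit four standards and each of 34 BEmOC facilities audit two. Under Target number of participants, for every facility and standard, "care received by 25 clients will be assessed in each of three study months". The Randomisation section randomises facilities to quarter 1 or 2 for each standard and aims for a balanced design.

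**The concern.** In a single-standard data set, the facility effect carries the correlation between the three measurements of that standard. In pooled data it no longer does. One facility intercept then stands for two or four standards whose compliance may differ widely; Appendix 1 ranges from weighing the newborn to correct use of the partograph. Two sources of variation have no term of their own: differences between standards, and a facility being persistently better at one standard than at another.

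At stake is the trial's primary estimate. Each standard is measured before and after action in the same facility, and much of the design's efficiency comes from that pairing. A model that does not identify the standard cannot use it fully, and its reported standard error need not match the true one.

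**Working it through.** **1. How differences between standards enter the contrast.** Figure 1 and Table 3 of the protocol give, for a BEmOC facility with standard E in quarter 1 and F in quarter 2:
- control assessments: E, F, F
- intervention assessments: E, E, F

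The raw contrast contains (2E + F)/3 − (E + 2F)/3 = (E − F)/3. If E and F differ by 30 points (illustrative), that facility contributes 10 points unrelated to the audit. For the CEmOC facility of Table 2 (A and C first, then B and D) the same step gives (A + C − B − D)/6. Quarter is randomised within standard, so these contributions average to zero over allocations. They are noise, not bias.

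**2. Reproducing the plan's own figure.** The protocol gives no precision figure for the pooled analysis. For one standard (18 facilities, 25 clients, ICC 0.2, CAC 0.5, 80% power, start 50%) Table 4 gives 21.6%. I used generalised least squares on the six sequences of Figure 1 with fixed months. The variance of a facility-month mean is ICC + (1 − ICC)/25 and the covariance within a facility is ICC × CAC, both per unit outcome variance. The variance of the effect is then 0.02622 per unit outcome variance. Solving d = (1.96 + 0.842) × √{0.02622 × [0.25 + (0.5 + d)(0.5 − d)]/2} gives d = 0.216. All Table 4 rows with 25 clients reproduce within about 0.2 points.

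**3. The pooled layout.** There are 10 × 4 + 34 × 2 = 108 facility-standard pairs, and 108 × 3 = 324 cells of 25 clients. This agrees with the stated total: 324 × 25 = 8,100.

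*From the protocol:* ICC 0.1 or 0.2, CAC 0.5 or 0.8, compliance 50% (total variance 0.25).

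*Assumed, not in the protocol:*
- 9 standards in use
- month variance 0.001
- share h of the cluster variance common to all standards in a facility: 0, 0.5 or 0.9
- between-standard variance 0 or 0.03 (SD 0 or √0.03 = 17 points)
- the same effect for every standard
- a linear approximation to the logistic model

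*Components:* with b = 0.25 × ICC × CAC and w = 0.25 × ICC × (1 − CAC), they are facility hb, facility-by-standard (1 − h)b, facility-by-month hw and facility-by-standard-by-month (1 − h)w. Sampling variance per cell is 0.25(1 − ICC)/25.

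*Comparison:* let V be the true covariance. Let W be the covariance fitted with facility, month and facility-by-month only, at its expected-REML values. X is the same throughout (intercept, facility type, intervention).
- Reported SE: root of the intervention entry of (X′W⁻¹X)⁻¹
- True SE: root of the same entry of HVH′, with H = (X′W⁻¹X)⁻¹X′W⁻¹
- SE with the terms: root of the same entry of (X′V⁻¹X)⁻¹
- Coverage: 2Φ(1.96 × reported/true) − 1

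Month is random on both sides, so the comparison isolates the missing terms.

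Selected results, quarters balanced within standard:

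| ICC | CAC | h | Between-standard variance | Reported SE | True SE | Reported/true | Coverage | SE with terms | True/with terms |
|---|---|---|---|---|---|---|---|---|---|
| 0.2 | 0.8 | 0 | 0 | 0.0238 | 0.0290 | 0.82 | 89% | 0.0203 | 1.43 |
| 0.2 | 0.8 | 0 | 0.03 | 0.0273 | 0.0289 | 0.95 | 94% | 0.0203 | 1.42 |
| 0.2 | 0.8 | 0.5 | 0.03 | 0.0258 | 0.0256 | 1.01 | 95% | 0.0211 | 1.21 |
| 0.2 | 0.5 | 0.5 | 0 | 0.0274 | 0.0289 | 0.95 | 94% | 0.0271 | 1.07 |
| 0.1 | 0.5 | 0.9 | 0 | 0.0224 | 0.0226 | 0.99 | 95% | 0.0225 | 1.00 |
| 0.1 | 0.8 | 0.9 | 0.03 | 0.0220 | 0.0196 | 1.12 | 97% | 0.0185 | 1.06 |

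Over all 24 combinations, reported/true runs from 0.82 to 1.12 and true/with terms from 1.00 to 1.43. In the first row the 95% half-width would be reported as 1.96 × 2.38 = 4.7 points. It should be 1.96 × 2.90 = 5.7 for that estimator, and could be 1.96 × 2.03 = 4.0 with the terms.

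With quarters left unbalanced (up to 7 facilities' difference for a standard; CAC 0.8 and h = 0.5 only), reported/true was 0.84 to 0.89 and true/with terms 1.12 to 1.44.

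**4. Simulation check.** I took a simulation on the linear scale with 200 runs per scenario, ICC 0.2, CAC 0.8, h = 0.5 and 8 standards (assumed). Empirical SDs without and with the terms were:
- 2.3 and 1.6 points with quarters random and between-standard SD 15 points
- 2.2 and 1.9 with quarters balanced
- 2.1 and 1.8 with no between-standard variance

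Reported/true was 0.95 to 0.98 and type I error 5% to 7%.

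**The case against.** The strongest reply is that the omission is inferred. A single-standard model has no use for a standard term, and a similar manner may mean the same class of model, not the same list. The equal weighting in the primary outcome definition would also fit a weighted combination of the per-standard estimates, and an analysis plan not shown may settle the matter. This stands to a degree: the protocol does not exclude the terms. But it does name the effects and refers the primary analysis to them, and followed literally they do not suit pooled data. A combination of per-standard estimates would also need a rule for the correlation between standards in one facility, and none is given.

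Three stronger readings are tempting and are not supported.
- *The standard error is too small.* This is not general. All standards measured in a given facility-month have the same intervention status, so the facility-by-month effect absorbs part of the omitted variation, sometimes more than is needed. A simulation of one configuration with 150 runs gave about 11% type I error, but its 95% interval is roughly 7% to 17%, and the results above go both ways.
- *The estimate is biased by differences between standards.* Randomising quarter within standard leaves chance imbalance only.
- *The variance is nearly tripled.* In that same simulation, true SDs of 4.0 against 2.4 points arise if months are fixed and the standard terms are still left out. The protocol plans random months. Against the model as listed, the figures were 2.7 and 2.4, a variance ratio of (2.7/2.4)² = 1.27.

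**Conclusion.** The point holds in this form. The only effects the protocol names for its primary analysis are those of a single-standard model. On pooled data they lose precision (true SE 0% to 43% larger with quarters balanced) and give an interval whose coverage could lie anywhere from about 89% to 97%.

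The loss is largest when most cluster variation is specific to the standard and stable over time. It almost vanishes when a facility performs alike on all its standards. The protocol gives neither the share of cluster variation common to standards nor the variance between standards, so the direction of the interval error cannot be known in advance.

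The sizes rest on the assumptions listed and on a linear approximation. The SE with the terms takes the variance components as known and standard as random, which is the best case for the fuller model. Pooled standard errors of 2 to 3 points are small beside the 22 points quoted for a single standard, so the matter is the validity and efficiency of the primary interval, not the ability to detect an effect of that size.

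**What to change.** State the pooled primary model in its own sentence:
- keep the effects already listed
- add standard as a fixed effect
- add random effects for facility-by-standard and facility-by-standard-by-month
- report the intervention effect so that each facility-standard pair keeps the equal weight set under Primary outcome measure

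Whether month should be fixed or random is a separate question, and this change does not depend on it.

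The cost is wording and a somewhat larger logistic mixed model. That model may need convergence work, so an order in which to simplify the random effects should be fixed before the data are analysed. No new data are needed.
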